**Methods/Design:**

All smokers with PTSD, regardless of their desire to quit, were invited to participate. Enrollment occurred between November 2009 and April 2013. Target enrollment was 120 participants. Enrolled participants were randomized to either the control group, receiving usual care including a telehealth PTSD program, with a device that delivered PTSD information and in-home care management, or the intervention group, which included (1) a telehealth PTSD program, (2) motivational interviewing-based smoking cessation curricula via the telehealth device, and (3) weekly motivational interviewing counseling phone calls. Outcomes are self-reported 24-hour quit attempts, progression along the stages of change and 7-day point prevalence quit smoking rates for the intervention group compared to usual care alone. Secondary outcomes include participants’ perception of care coordination, patient satisfaction with motivational interviewing, PTSD symptoms, pain, depression and quality of life.

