## Methods/Design

### Study design overview

This single center randomized trial is funded by the Department of Veterans Affairs Health Services Research and Development Service. It tests the effectiveness of integrated care management using telehealth and MI telephone counseling for smoking cessation treatment for Veterans with PTSD (Figure 1). A total of 120 participants were targeted for enrollment. Primary outcomes are self-reported quit attempts as measured by 24-hour point prevalence, perception of care coordination, and PTSD symptoms. Additional outcomes include progression along the stages of change and 7-day point prevalence quit rate. Outcome data will be measured at the end of the intervention period (month 3) and 6 months post-intervention (month 9). This study followed all applicable IRB regulations and was approved by the Colorado Multiple Institutional Review Board.

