Sample size calculations were based on testing the effectiveness of the intervention, compared to the control group, in higher rate of quit attempts and progression in the stage of change, better perceived care coordination, and improved PTSD symptoms. Only the trend of quit rate differences will be examined since the study sample will include those who are not ready to quit. Initially we expected to enroll 140 subjects in order to obtain 120 completers, anticipating a 12-15% drop out rate. However, due to a higher than expected loss to follow up rate enrollment was expanded to target 180 participants. Statistical analyses will be done using SAS (Cary, NC). Objective one involves comparison of two proportions for self-reported quit attempt rate and stage change rate. With 120 subjects, equally allocated between the two groups, 24% absolute difference in rates at 3 months can be detected for a two-sided test of proportions between two groups at a 5% Type I error rate and 80% power. Objective two and three involve comparison of means across two groups for perceived care coordination and PTSD symptoms. Effect size of 0.1, 0.25 and 0.4 (or equivalently mean difference of 0.2, 0.5, 0.8 in standard deviation units between two groups) are typically defined as small, medium, and large. By recruiting the 120 subjects for objective one, a medium effect size in perception of care coordination and PTSD symptoms can be detected for a two-sided test of means between two groups at a 5% Type I error rate and 80% power. We will consider this finding to be clinically significant if intervention group Veterans perceive their care to be better coordinated and they experienced less PTSD symptoms.

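### The abstract and design overview give 120 as the enrolment target, but the sample-size paragraph makes 120 the completers, with 180 to enrol; and 60 completers per arm give about 77.5% power at 0.5 SD, slightly below the stated 80%

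*Protocol article*

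**What the plan says.** **Enrolment.** The abstract (Methods/Design) says "Target enrollment was 120 participants". The Study design overview says "A total of 120 participants were targeted for enrollment". The sample-size paragraph under Outcome measures gives a different account: 140 were to be enrolled at first so that 120 would complete, allowing for 12-15% dropout; then "due to a higher than expected loss to follow up rate enrollment was expanded to target 180 participants". Later in that paragraph the number 120 appears again as the number recruited: "By recruiting the 120 subjects for objective one, a medium effect size in perception of care coordination and PTSD symptoms can be detected".

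**Means (objectives two and three).** A medium effect is defined there as 0.5 SD. The claim is that "a medium effect size in perception of care coordination and PTSD symptoms can be detected for a two-sided test of means between two groups", with a 5% type I error rate and 80% power. Data analysis names Student's t-test as the first test, followed by a multiple linear regression.

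**Proportions (objective one).** "With 120 subjects, equally allocated between the two groups, 24% absolute difference in rates at 3 months can be detected", again at two-sided 5% and 80% power. No control-group rate accompanies the figure. Data analysis names the chi-square test.

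**The concern.** The number 120 has two meanings in current text: the number to be enrolled (abstract, overview, and the wording about recruiting in the sample-size paragraph) and the number to complete (the dropout allowance in that same paragraph). By the dropout account, 120 was neither the initial nor the final enrolment target.

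A reader needs to know which meaning applies in order to judge recruitment against target and to read the power statement. Under intention to treat, with non-responders counted as continuing smokers, the number enrolled also bears on the denominator for the smoking outcomes.

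The means claim has every input fixed, so it can be checked exactly. It concerns perception of care coordination and PTSD symptoms, which are the primary outcomes of objectives two and three. If the stated 80% is not reached, a null result on either would be read against a slightly optimistic figure.

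**Working it through.** **1. The enrolment numbers**

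| Place in the protocol article | Number | Role given to it |
|---|---|---|
| Abstract, Methods/Design | 120 | enrolment target |
| Study design overview | 120 | enrolment target |
| Outcome measures, sample size | 140 | initial enrolment, to yield 120 completers |
| Outcome measures, sample size | 180 | expanded enrolment target |
| Outcome measures, sample size | 120 | completers, then subjects recruited |

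The dropout arithmetic shows which meaning the calculation used. 120 / (1 - 0.12) = 136.4, so 137. 120 / (1 - 0.15) = 141.2, so 142. The stated 140 lies between them, so 120 entered as completers. If 120 completers is still the aim at 180 enrolled (implied, not stated), the allowance is 1 - 120/180 = 33.3% loss.

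**2. Means**

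Inputs, all from the document: n = 60 per arm, difference d = 0.5 SD, two-sided alpha 0.05, Student's t-test, stated power 80%.

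- Normal approximation: power = Phi(d x sqrt(n/2) - 1.960) = Phi(0.5 x sqrt(30) - 1.960) = Phi(0.779) = 78.2%.
- Noncentral t with 118 degrees of freedom and noncentrality 0.5 x sqrt(30) = 2.739: power = 77.5%.
- Number for 80%, normal approximation: 2 x (1.960 + 0.842)^2 / 0.5^2 = 62.8, so 63 per arm (126 in total).
- Number for 80%, t-test: 64 per arm (128 in total; power 80.15%). At 63 per arm it is 79.5%.
- Difference detectable at 80% with 60 per arm: 2.802 x sqrt(2/60) = 0.511 SD (normal approximation), or 0.516 SD (t-test).

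The stated 80% is missed by 1.8 points with one method and 2.5 points with the other, which is 6 to 8 subjects in total.

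**3. Proportions (minor remark)**

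Inputs: n = 60 per arm, difference 0.24, two-sided alpha 0.05. The control rate p1 is not stated, so it is varied as an assumption. With p2 = p1 + 0.24 and pm = (p1 + p2)/2:

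power = Phi{[0.24 - 1.960 x sqrt(2 pm (1 - pm)/60)] / sqrt([p1(1 - p1) + p2(1 - p2)]/60)}

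| Control rate | Intervention rate | Power |
|---|---|---|
| 10% | 34% | 89.8% |
| 20% | 44% | 81.3% |
| 25% | 49% | 78.5% |
| 30% | 54% | 76.6% |
| 38% | 62% | 75.5% (minimum) |
| 50% | 74% | 78.0% |
| 55% | 79% | 80.6% |

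Worked at 38%: pm = 0.50, so the standard error is 0.0913 pooled and 0.0886 unpooled, and (0.24 - 0.1789)/0.0886 = 0.689, giving 75.5%. Power is at least 80% for control rates up to about 22% or from about 54%. The stated figure therefore reproduces for some control rates and not for others. The limits also move with the formula: using the unpooled variance throughout, 25% versus 49% gives 80.3%.

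**The case against.** *The means shortfall is immaterial.* The document claims only that a medium effect is detectable, on a scale of 0.2, 0.5 and 0.8, and 0.516 rounds to 0.5. The number was chosen for objective one. The planned regression should also gain precision: if baseline variables had a correlation of 0.3 with the outcome (an assumed value, not in the document), power would be about 81%. What stands is that the gap is small and gives no reason to redesign. But the sentence claims 80% for a two-group test of means, and neither method reaches that at 60 per arm.

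*The sample-size paragraph explains itself.* A reader might infer that 120, 140 and 180 are three conflicting targets. They are not: 140 and then 180 form a sequence with a stated reason, and the 140 reproduces. The contradiction is only between 120 as enrolled and 120 as completers. A careful reader can resolve it from the sample-size paragraph, but not from the abstract or the overview alone.

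*The 24 points cannot be shown wrong.* This stands. The sample includes smokers not ready to quit, so a low control rate is plausible, and a condensed article may leave that rate to the full protocol.

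*A much weaker trial.* A reader who takes 120 as enrolment might apply 12-15% loss, reach 51 to 53 per arm, and conclude that power falls well below 80% on every endpoint. The document does not support this. Enrolment was set above 120 precisely to cover loss. For the smoking outcomes, non-responders are classified as smokers and stay in the denominator, so loss would act by diluting the effect and not by shrinking the sample.

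**Conclusion.** The enrolment contradiction holds on the text alone: 120 is the enrolment target in two places and the number of completers in the paragraph that derives it. The power statement for means is slightly overstated: 77.5% by the planned t-test (78.2% by the normal approximation) against a stated 80%, or 0.516 SD against 0.5 SD. This rests on 60 completers per arm, equal allocation and the unadjusted test.

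It would go too far to say that 80% power is not met at 120 subjects for the trial as a whole. For proportions the result depends on an unstated control rate. Power could be as low as 75.5% near a control rate of 38%, but it is 80% or more up to about 22% and from about 54%. All that can be said is that the 24-point figure cannot be checked without that rate.

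**What to change.** - In the abstract and the Study design overview, say that the enrolment target was expanded to 180 and that 120 is the number of completers on which power is based.
- In the sample-size paragraph, replace the wording about recruiting 120 subjects with 120 completers.
- Restate the means claim for 60 completers per arm: about 0.52 SD detectable at 80% power, or about 77-78% power at 0.5 SD.
- Give the control rate assumed for the 24-point difference. If quit attempts and stage change had different assumed rates, give both.

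These are text corrections. They change neither design nor analysis; the only cost is a slightly less favourable power statement for the means.

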### Data collection

Outcomes are assessed at the end of the intervention period (month three) and six months post-intervention (month 9). Data collection occurs at baseline, at set points during the intervention period, at the end of the intervention period (month 3), at set points during the follow-up period, and six months post-intervention (month 9). Many survey questions are entered into the Health Buddy program and then answered by the participants via the appliance. Each subject will attend an in-person study visit at designated times to complete surveys not able to be performed via the Health Buddy. A small incentive will be given to subjects (total of $24 for three visits) to help defray associated costs.

Baseline data include expired carbon monoxide level, McGill Pain Questionnaire (both done at in-person enrollment), PACIC, PTSD Checklist, Stage of Change, Fagerström Test of Nicotine Dependence [36], GDS, and VR-12. As these surveys, except when noted, are implemented via the Health Buddy and done at home by the participant, not all baseline survey results are recorded on the day of enrollment.

During the intervention period, a 24-hour cigarette recall is asked via the Health Buddy weekly. Stage of change and suicide risk are assessed monthly via the Health Buddy during the intervention portion of the study. At the end of the intervention period, the following data are collected: expired carbon monoxide level, McGill Pain Questionnaire (both done in person), PACIC, PTSD Checklist, Stage of Change, GDS, and VR-12. Participant satisfaction with the MI written content and the MI counseling calls is assessed at this time, as well. Unless otherwise noted, surveys are completed on the Health Buddy and therefore all participants do not complete them on the same day; it is dependent on how many days a week the Health Buddy is used by a participant.

During the six month follow-up period, stage of change and a 24-hour cigarette recall are asked monthly. At the end of the six-month follow-up, participation in the study ends and the following additional data are collected: expired carbon monoxide level, McGill Pain Questionnaire (both done in person), PACIC, PTSD Checklist, Stage of Change, GDS, and VR-12.

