**Conceptual model.**

Participants are asked to use the research Health Buddy daily for 90 sessions (the intervention period). During the follow up period (final six months), monthly calls are made by the research staff to gather smoking data. If any participant wants to continue to use the Health Buddy after the intervention period, the individual’s telehealth care is transferred to the VHA’s Care Coordination Home Telehealth Department and they use the standard PTSD Health Buddy program.

All participants have access to usual tobacco cessation care at the VHA, which includes a specialty tobacco cessation clinic, a tobacco cessation support group in the mental health clinic, a month long tobacco cessation educational group, and/or treatment within the primary care setting. All first line medications are available to study participants, including bupropion SR, nicotine gum, nicotine lozenge, nicotine patch. Varenicline, nicotine nasal spray and nicotine inhaler use is restricted by the VHA for use by those who failed other medication therapies. In order to utilize existing treatment modalities, study nurses assess participants’ desire to use a medication and, if interested, a referral is made to existing providers.

Consistent with MI principles, participants will make choices about how and when to participate. We acknowledge that not all participants will chose to answer the Health Buddy questions daily or to be available for their counseling call weekly.

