#### Motivational interviewing counseling

The intervention group will participate in weekly counseling calls. Interactions with the research nurse are based on stage of change and responses to the home telehealth smoking cessation curriculum. MI techniques such as 1) giving advice as requested, 2) removing barriers, 3) providing choice, 4) decreasing desirability, 5) practicing empathy, 6) providing feedback, 7) clarifying goals, and 8) actively helping [15,24] are utilized. MI techniques will vary based on stage of change. For example, the individual in pre-contemplation is not currently considering a change. The care coordinator will validate lack of readiness, respect autonomy, encourage re-evaluation, and ask permission when explaining risks.

To ensure fidelity, random calls made by the intervention research nurse are observed throughout the study. Additionally, the research nurse will participate in ongoing MI training and workshops throughout the study to diminish “drift” away from the principles of MI.

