### Outcome measures

The study has three objectives; each has a primary outcome and secondary endpoints. Secondary outcomes are exploratory and supportive of the primary outcomes.

In objective one, we will compare the (1) proportion of individuals that make a self-reported 24-hour quit attempt, (2) progression through the stages of change [25,26] and (3) 7-day point prevalence quit smoking rates for the intervention group to usual care alone. The primary outcome is the proportion of participants making a self-reported quit attempt in each group during the study period. Secondary outcomes are the proportions of individuals who make a progression in their stage of change and quit smoking, as measured by a 7-day point prevalence, between study entry, end of intervention (month 3) and at 6 months post-intervention (month 9). Quit attempts will be bioverified by expired carbon monoxide levels (a CO level of less than or equal to ten will be considered non-smoking) [27] during in-person visits at the 3 month and 6 month follow-up periods. Subjects who do not respond will be classified as continuing smokers.

In objective two, we will compare the patient perception of care coordination for the intervention group to usual care alone. The primary outcome is the mean score change of the participant’s perception of care coordination (PACIC) [28,29] from baseline to end of intervention (month 3), and 6 months post-intervention (month 9) periods. Secondary endpoints of interest are an evaluation of the intervention from the participants’ perspective via two satisfaction surveys (one for stage-based/MI smoking cessation Health Buddy written content and one for the nurse-driven MI intervention). Patient satisfaction will be evaluated for the intervention group only at the end of the intervention (month 3).

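### If the primary outcome counts any quit attempt, collecting it in months 0–3 by a recall on the Health Buddy ties the result to device use, which may differ by arm

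*Protocol article*

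**What the plan says.** Outcome measures defines the objective-one primary outcome cumulatively: "The primary outcome is the proportion of participants making a self-reported quit attempt in each group during the study period". Study design overview describes it differently: "Primary outcomes are self-reported quit attempts as measured by 24-hour point prevalence". Data analysis compares quit attempts between arms at the end of the intervention (month 3) and six months later (month 9).

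Data collection gives the source for months 0–3: "During the intervention period, a 24-hour cigarette recall is asked via the Health Buddy weekly". The other smoking-related item in that period is on the same device: "Stage of change and suicide risk are assessed monthly via the Health Buddy during the intervention portion of the study". The month-3 list reads "expired carbon monoxide level, McGill Pain Questionnaire (both done in person), PACIC, PTSD Checklist, Stage of Change, GDS, and VR-12. Participant satisfaction" and goes on to the satisfaction surveys. Its off-device items are carbon monoxide and the pain questionnaire, and neither asks about quit attempts. For surveys answered on the device, the article says of the day of completion that "it is dependent on how many days a week the Health Buddy is used by a participant".

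The Intervention section expects incomplete use: "We acknowledge that not all participants will chose to answer the Health Buddy questions daily or to be available for their counseling call weekly". It also says that research staff telephone monthly for smoking data, but only in the six-month follow-up. Both arms have the device. Only the intervention arm has the smoking curriculum on it and the weekly counselling calls, of which the article says: "Interactions with the research nurse are based on stage of change and responses to the home telehealth smoking cessation curriculum".

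**The concern.** With an outcome of the kind 'ever recorded', each answered recall is another chance to be counted. A participant who stops using the device in week 4 and goes a day without smoking in week 8 has, on the listed schedule, no occasion to report it. The follow-up calls ask about the last 24 hours only, so they do not recover that day.

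If the arms answer different numbers of recalls, the recorded proportions separate even when true behaviour is identical. The planned logistic regression adjusts for baseline variables, and the number of answered recalls arises after randomisation. Classing non-responders as continuing smokers does not help either: applied to a missed recall, it turns 'not asked' into 'no attempt'. Larger enrolment would estimate the same artefact more precisely. What is at stake is whether a difference in the primary outcome can be read as a difference in quitting behaviour rather than in device use.

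**Working it through.** **1. The plan's own figure.** The article states that 120 participants (60 per arm) can detect a 24-point difference at 3 months with two-sided 5% error and 80% power. It gives no control rate. Assuming 20% versus 44%, the normal-approximation test of two proportions gives power of 81.3% and needs 59 per arm, so the figure reproduces. At control rates of 38–40% the detectable difference is about 25 points.

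**2. Model with no true effect.** Let q be the chance that an answered weekly recall shows a smoke-free 24 hours, the same in both arms, and k the number answered. With independent weeks and unanswered recalls counted as no attempt:

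P(recorded as attempter) = 1 − (1 − q)^k

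The 90 daily sessions span 90/7 ≈ 13 weeks, so about 13 recalls are offered. The article gives neither q nor answer rates by arm. All values below are assumptions.

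**3. Illustration at month 3.** Suppose 80% versus 60% of recalls are answered: k = 0.8 × 13 = 10.4 and k = 0.6 × 13 = 7.8.

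| q | k = 10.4 | k = 7.8 | Spurious gap |
|---|---|---|---|
| 3% | 27.2% | 21.1% | 6.0 points |
| 5% | 41.3% | 33.0% | 8.4 points |
| 10% | 66.6% | 56.0% | 10.5 points |

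For example, 1 − 0.95^10.4 = 0.413 and 1 − 0.95^7.8 = 0.330. With equal k the gap is zero at every q.

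**4. Effect on the test.** At q = 5% with 12 versus 8 answered recalls, the recorded rates are 46.0% and 33.7%, a gap of 12.3 points. A nominal 5% chi-square test at 60 per arm then rejects about 28% of the time (28.4% by simulation), and about 39% at 90 per arm. With 12 versus 10 the gap is 5.8 points and rejection about 9%. With 12 versus 12, rejection is about 5%.

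**5. What makes it smaller.**
- *Clustering.* Let q vary between people (beta-binomial, mean 5%). With an assumed within-person correlation of 0.09, 0.20 or 0.33, the 8.4-point gap falls to about 5, 3 or 2 points.
- *Follow-up calls.* Add six answered monthly recalls in each arm, so k = 16.4 versus 13.8. At q = 5% with independent weeks, 1 − 0.95^16.4 = 56.9% and 1 − 0.95^13.8 = 50.7%. The gap is 6.2 points.

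The month-9 result is therefore diluted but not freed of the problem, and month 3, the time point used for sizing, has no such dilution.

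**The case against.** Four objections carry weight.

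*The list may be incomplete.* Outcome measures requires a 7-day point-prevalence quit rate, yet Data collection names no 7-day item. A condensed article may also have left out a quit-attempt question at the visits. This stands as a caveat: the point concerns the schedule as described.

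*The mechanism needs the cumulative definition.* If the outcome is whether the participant was smoke-free in the 24 hours before month 3 or month 9, the number of accumulated recalls does not drive it. Study design overview and Data analysis can be read that way, and Outcome measures cannot easily be. The point is conditional on the latter.

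*Unequal use is not shown.* Both arms have the device and care coordination, with a coordinator reading responses daily. The text on counselling says what shapes the calls, not that they prompt device use. Daily smoking content given to people who may not wish to quit could also put them off the device. A reader might infer that the trial is biased towards the intervention; the documents do not support that, because they give no use by arm.

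*The sizes rest on a simple model.* Independent weeks and one common q give the larger gaps. This is right, and the reductions are shown above.

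None of this removes the dependence itself. On the listed schedule, being counted in months 0–3 requires answering on the device, and the article expects incomplete answering.

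**Conclusion.** The point holds conditionally. As the article describes it, and if any attempt during the study counts, a difference in device use between arms would by itself produce a difference in the objective-one primary outcome. Unequal use is plausible because smoking content and weekly calls are confined to one arm. Its direction and size are unknown.

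The 8-point figure (q = 5%, 10.4 versus 7.8 answered recalls, independent weeks) illustrates scale against the 24 points the trial was sized for. It does not estimate the bias in this trial. The gap is about 2 to 5 points under the assumed clustering, about 6 once six follow-up calls are added, and zero if use is equal. A reader might take these figures as evidence that a positive result would be spurious; they are not. This is a weakness in ascertainment that is cheap to remove, not a demonstrated bias.

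**What to change.** At the existing month-3 and month-9 in-person visits, ask every participant in both arms, whether or not they still use the device, whether they made any quit attempt of at least 24 hours since the previous visit. Base the primary outcome on that answer, and say so in Outcome measures and Data collection. Keep the weekly device recall as supportive data and report the number of answered recalls by arm.

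The cost is one question at visits already scheduled. The downside is longer recall: about three months at the first visit and six at the second. The change removes dependence on device use but not on attending the visit. It is preferable to replacing the weekly recalls with about three monthly 24-hour recalls, which at q = 5% would cut the recorded proportion from 1 − 0.95^13 = 49% to 1 − 0.95^3 = 14%.

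Enrolment ran to April 2013, so the month-3 item may come too late for many or all participants. For those already past month 3, report answered recalls by arm, add a sensitivity analysis restricted to answered weeks (for example, the proportion of answered recalls that were smoke-free), and state the limitation. That analysis assumes that answered weeks represent unanswered ones.
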